### Procedure

Women being offered BC-Predict will be sent an invitation letter one to two working days after their breast screening invitation letter is sent. The BC-Predict invitation letter will be sent along with the participant information sheet and instructions directing prospective participants to the online risk assessment platform. Each invitation letter will include details of the participant’s “Date of first offered appointment”. This is the first breast screening appointment date that was offered to the participant. This date is of relevance because participants will be able to join the study either before the date of their first offered appointment or up to six-weeks after. After this time it will no longer be possible for them to login to the BC-Predict risk assessment platform. Prospective participants will be directed to telephone the study helpline if they have any questions, or if they require any further information prior to deciding whether or not to take part. The timeline from the participant perspective is shown in Fig. 1. An overview of data-flows is shown in Fig. 2.

**Fig. 1 Fig1:**
[figure not shown]
Timeline of Psychological-Impact study integrated with BC-Predict and NHSBSP

**Fig. 2 Fig2:**
[figure not shown]
Study Participant Data Flow Diagram

Once participants have consented to the study online, they will be directed to the BC-Predict risk assessment questionnaire. Participants will be able to enter part of the questionnaire, save and return to it at a later date, as long as they do this within their six-week recruitment window. Assessment of the online questionnaire during the pilot phase estimated that most women would be able to complete this within 30 min. If a prospective participant doesn’t have access to the internet, a paper version of the questionnaire can be posted out to be completed along with a paper version of the consent form. The data recorded on the questionnaire will then be manually inputted into the online risk assessment platform by a member of the study team, and the standard process will be followed from this point.

Once a clear mammogram result has been provided, a risk feedback letter is generated based on the answers participants give in their questionnaire and mammographic breast density (calculated from uploaded raw data by Volpara systems). The percentage density is inserted into an online version of Tyrer-Cuzick v8 that includes an algorithm to adjust density for age BMI and menopausal status in into an odds ratio known as density residual [14]. The risk feedback letter will inform women that they are at “high” (≥8% 10-year risk), “moderate” (≥5% but < 8% 10-year risk), “average” (≥ 2% but < 5% 10-year risk), or “below average” risk (< 2% 10-year risk). Each letter will explain how the risk estimates were derived, and the implications of these. Each group of women will receive this letter in the post, along with a leaflet providing additional detail on breast cancer risk factors, signs and symptoms of breast cancer and how risk might be managed. Those women who complete the BC-Predict risk assessment questionnaire over the telephone will also be sent copies of this questionnaire so that they can check for data entry errors and the electronic consent form for participant’s records.

All BC-Predict participants will have been invited for breast screening but a proportion may choose not to attend their breast screening appointment; attendance at breast screening mammogram is not a compulsory part of the study. The Participant Information Sheet explains that participants’ mammographic breast density will be included in their risk assessment, providing they attend their mammogram within 6-weeks of their first offered appointment. It is also explained that including mammographic density increases accuracy of the risk assessment. Any participant who declines a mammogram or has a mammogram after this time will not have this data included in their risk assessment, which is explained in their risk feedback letter.

To assess self-reported harms and benefits, and to inform an economic analysis, a randomly selected subsample of *n* = 2108 women (*n* = 1054 each from usual care NHSBSP and BC-Predict) will be asked to complete questionnaires assessing psychological benefits and harms of BC-Predict at baseline, 3-months and 6-months. For women in both groups, the request to complete the questionnaire will be sent shortly after their mammography invitation but before their first offered mammogram appointment, asking for their help in evaluating a new approach to providing NHS breast screening. They will be given instructions to complete an online consent form and questionnaire using their unique study identification number on SmartSurvey (https://www.smartsurvey.co.uk/). The same women will be asked to complete the questionnaire three and 6 months after their first offered mammogram appointment. Women in both experimental groups will only receive follow-up questionnaires once they receive a clear mammogram result.

The risk assessment and feedback will take account of each patients’ journey through the NHSBSP. The study team will periodically check screening outcomes for participants. There are a number of initial screening outcomes: (a) clear mammogram and woman will be invited for routine breast screening in three-years (routine recall); (b) mammogram taken is technically inadequate so repeat mammogram is required (technical recall); (c): suspicious mammogram and further assessment required (recall for assessment). For all scenarios the GP will be informed of the participant’s involvement in the study and provided with their risk feedback.

Participants who are confirmed as having a routine recall screening outcome will receive their risk feedback after this, approximately 6 weeks after their mammogram. Participants who are invited for a technical recall/recall for assessment appointment, and attend this appointment within 6 months of their first scheduled technical recall/recall for assessment appointment, and who are subsequently confirmed as not having breast cancer will receive a risk feedback letter following confirmation of an absence of breast cancer. Participants who are invited for a technical recall or recall for assessment appointment but do not attend within 6 months of the first scheduled technical recall/recall for assessment appointment (i.e. those for whom there is no screening outcome within 6 months of initial screening outcome) will receive their risk feedback 6 months after joining BC-Predict.

Participants who do not attend a breast screening appointment within six-weeks of their first offered breast screening appointment will receive their risk feedback after this six-week period (i.e. 7 to 8 weeks since their first offered breast screening appointment).

Participants who are diagnosed with breast cancer will not receive a standard risk feedback letter. Participants will be sent a letter 1 year after diagnosis which will offer them feedback from the study. If they opt to receive this, they will be sent a personalised letter explaining their breast cancer risk factors.

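### The rule for women who do not attend recall uses three different six-month clocks, so for early joiners the feedback date falls before non-attendance can be established

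*Protocol article*

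**What the plan says.** All the relevant text is in the Procedure section of the protocol article (Methods/design).

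- **Joining.** The BC-Predict invitation follows the screening invitation by one to two working days, and "participants will be able to join the study either before the date of their first offered appointment or up to six-weeks after".
- **Recalled women who attend.** Those who "attend this appointment within 6 months of their first scheduled technical recall/recall for assessment appointment" and are found not to have breast cancer get their feedback once cancer has been ruled out.
- **Recalled women who do not attend.** The group is those who "do not attend within 6 months of the first scheduled technical recall/recall for assessment appointment". A bracket introduced by i.e. restates it as "those for whom there is no screening outcome within 6 months of initial screening outcome". These women "will receive their risk feedback 6 months after joining BC-Predict".
- **Diagnosed women.** "Participants who are diagnosed with breast cancer will not receive a standard risk feedback letter".
- **General condition.** Earlier in the same section: "Once a clear mammogram result has been provided, a risk feedback letter is generated".

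The recalled group has two parts: technical recall, where the image was inadequate, and recall for assessment, where the mammogram was suspicious.

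**The concern.** One rule for one group of women has three start dates: the first scheduled recall appointment, the initial screening outcome, and joining the study. The bracket presents the first two as equivalent. They are not, because the appointment comes after the outcome that prompts it. The third can precede both, since a woman may join before she has been screened.

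For such a woman, the date on which feedback is due arrives while she still has time to attend and so move into the other group. Non-attendance is the condition for releasing the feedback, and on that date it cannot yet be known. If the date is honoured anyway, she receives a risk letter with her recall unresolved. If she then attends within her window and is diagnosed, she already holds feedback that the article says diagnosed women are not sent. If the date is not honoured, the protocol is not being followed as written. BC-Predict is described as an automated system that generates letters, so some release date has to be implemented, and the text does not fix one that works.

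**Working it through.** There is no figure in the plan to reproduce; the check is date arithmetic.

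**Definitions.** Day 0 is the first offered appointment. J is the day of joining, O the day of the initial screening outcome, R the day of the first scheduled recall appointment. Six months is taken as 182.5 days.

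- Feedback due = J + 182.5
- Clock in the bracket ends = O + 182.5
- Attendance window closes = R + 182.5
- Days the window is still open when feedback falls due = (R + 182.5) − (J + 182.5) = R − J

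**Direction.** This needs no assumption about intervals. R follows the mammogram. Any woman who joins before her mammogram has J < R, so her feedback falls due before her window closes. The order reverses only when J > R, that is, when she joins after her recall appointment date.

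**Size.** The times from mammogram to outcome and from outcome to recall appointment are not given. They are assumed here to be 7 to 21 days each. A mammogram on day 42 represents attendance six weeks after the first offered date.

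| Joins (J) | Mammogram | Outcome (O) | Recall appointment (R) | Feedback due | Bracket clock ends | Window closes | R − J |
|---|---|---|---|---|---|---|---|
| −21 | 0 | 21 | 42 | 161.5 | 203.5 | 224.5 | 63 |
| −14 | 0 | 14 | 21 | 168.5 | 196.5 | 203.5 | 35 |
| 0 | 0 | 7 | 14 | 182.5 | 189.5 | 196.5 | 14 |
| −21 | 42 | 63 | 84 | 161.5 | 245.5 | 266.5 | 105 |
| 0 | 42 | 49 | 56 | 182.5 | 231.5 | 238.5 | 56 |
| 42 | 0 | 21 | 42 | 224.5 | 203.5 | 224.5 | 0 |
| 42 | 0 | 14 | 21 | 224.5 | 196.5 | 203.5 | −21 |

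For joining between day −21 and day 0, the window is still open for 14 to 63 days with a mammogram on day 0, and for 56 to 105 days with a mammogram on day 42. The last two rows show that late joining does not by itself reverse the order. Joining on day 42 gives no gap if the recall appointment is also on day 42, and a reversal of 21 days if it was on day 21.

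The bracket does not resolve the conflict. In the second row its clock ends on day 196.5, which is 28 days after feedback is due (196.5 − 168.5) and 7 days before the window closes (203.5 − 196.5).

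**The case against.** The strongest reply is that the text sorts recalled women by a single test, attendance within 6 months of the first scheduled recall appointment, so the two groups cannot overlap. The release clause applies only to women who have failed that test, and a woman whose window is open has not failed it. A reader might infer that the same woman must both wait for cancer to be excluded and be sent her feedback. The documents do not say that, and this part of the reply stands. What it leaves untouched is that, for an early joiner, the stated release date passes before the test can be completed. The statements that letters follow a clear result, and that the team checks screening outcomes periodically, fit holding the letter back better, but neither settles which clock governs. Fig. 2, the data-flow diagram, is not available here.

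Three further points also stand:

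- Part of any false reassurance comes from the stated decision to send feedback to women who never attend recall. Under any single clock such a woman would receive a letter, and could still attend and be diagnosed later. That decision is not challenged here.
- A reader might infer that diagnosed women would be misclassified in the data. Under Core outcomes, diagnoses for BC-Predict participants come from NHSBSP and clinic records, not from the type of letter sent. No comparison is shown to change.
- Not every woman concerned has a suspicious mammogram, since technical recalls are included.

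**Conclusion.** The inconsistency is real, and nothing in the article resolves it. For every recalled woman who joined before her mammogram and remains unassessed, the stated release date precedes the close of her attendance window by the time from joining to the recall appointment. The direction follows from the text alone. The size (35 days in the middle example, 14 to 63 days with a mammogram on the first offered date) rests on assumed intervals. The consequence is one of two things: a rule that cannot be followed on its stated date, or feedback sent while a recall is unresolved and attendance is still possible. The text does not show which would happen in practice.

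The stronger conclusion, that the protocol directs letters to women with unassessed suspicious mammograms during their attendance window and so causes direct harm, is not supported. It takes only one of the two branches, and an effect of the letter on attendance is plausible but not shown. The women concerned are consenting participants who were recalled and are still unassessed about six months after joining. Their number is not given and is probably small. Because the point bears on safety and is cheap to correct, it should be fixed, but it does not call the design into question.

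**What to change.** Reconcile the three clauses in Procedure so that the attendance window, its restatement in the bracket and the release of feedback run from one consistent start date, and feedback does not fall due before the protocol's own non-attendance condition can be established. Carry the same date into the letter-release logic of the BC-Predict platform. Which start date and what length to use is for the clinical team.

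The cost is about one sentence in the protocol and one date setting. The downside is that some women will receive their letter some weeks earlier or later than under the present wording.

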### Measures

Two main types of measures will be used: core outcome measures and self-reported measures.

#### Core outcomes

The following nine core outcomes will be compared at 6-months post completion of recruitment for those offered BC-Predict and those offered usual care (NHSBSP):

1. Screening attendance at first offered screening episode.

2. Screening attendance within 180 days of episode opening.

3. Number of technical recalls.

4. Number of recalls for assessment.

5. Number of routine recalls.

6. Number of breast cancer diagnoses (and type/grade).

7. Subsequent consultation in FHRP clinics (and mode: telephone or face-to-face).

8. Subsequent enrolment for more frequent screening.

9. Subsequent prescription of chemoprevention. Data will be collected on each of the following aspects of this: (a) participant agrees/disagrees in clinic to take chemoprevention, (b) chemoprevention not appropriate, (c) chemoprevention appropriate but prescription not filled, (d) chemoprevention appropriate and prescription filled.

Data for the nine core outcomes will be collected for each consented BC-Predict participant by the research staff for the 6 months following participants’ mammography appointment. For these participants, information will be available directly from NHSBSP and FHRP clinic records. For those in the usual care arm of the study, anonymised data will be provided by NHSBSP and FHRP services, to provide overall numbers for each of the core outcomes. We will prospectively record any refinements to procedures, to allow examination of how these impact on uptake of services.

We will also assess uptake of BC-Predict, and examine variation by study site. Where changes to recruitment procedures are made, we will keep notes of this, and examine the effects of these changes on uptake of BC-Predict, to inform how risk stratified screening should be rolled out. We will also examine variations in uptake of services by Index of Multiple Deprivation deciles derived from postcode of women [28] invited for NHSBSP, to assess any potential exacerbation of health inequalities brought about by BC-Predict.

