### Analysis plan and power calculations

#### Core outcomes

In total, approximately *n* = 18,700 women will be offered BC-Predict and *n* = 18,700 will be offered usual care NHSBSP over the total 16-month period. Based on the recruitment rate in PROCAS, *n* = 18,700 women being offered BC-Predict should result in 8000 women taking it up. The attendance rate to usual NHSBSP in Greater Manchester is 69% [5, 10].

Core outcomes will be compared for cohorts of women who are invited to BC-Predict and those who are invited to usual care (NHSBSP). Thus we will have in excess of 8000 participants in BC-Predict and NHSBSP groups for both comparisons: (a) within-site and (b) between sites over the same time period. The primary outcomes are binary. Logistic regression will be the primary statistical analysis method. We shall assess heterogeneity effects using interaction tests in the logistic regression, to examine differences in outcomes by time or location or screening type (prevalent v incident). Even in the presence of geographic or temporal heterogeneity of the effect, or of carryover effects continuing beyond the crossover period, we will still have sufficient data for a valid and fully powered comparison.

For core outcomes 1 and 2, we are interested in equivalence, in that we anticipate that invitation to BC-Predict will not substantially affect screening attendance. With 18,700 women in each group we will have in excess of 90% power to establish equivalence, defined as a 95%CI on the difference which does not exceed ±5% on the attendance rate at first offered appointment, if the latter is around 50% [37]. Similarly, we will have more than 90% power for the same comparison for eventual attendance within 180 days if the latter is around 70%.

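### Core outcomes are compared by invitation, but no data source is stated for the roughly 10,700 women invited to BC-Predict who are not expected to consent

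*Protocol article*

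**What the plan says.** The Analysis plan section (Core outcomes) sets the comparison by invitation: "Core outcomes will be compared for cohorts of women who are invited to BC-Predict and those who are invited to usual care (NHSBSP"). The Measures section likewise compares women offered BC-Predict with women offered usual care, and the Background lists lower programme uptake among women offered BC-Predict as a potential harm.

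For attendance (core outcomes 1 and 2) the aim is equivalence, because "we anticipate that invitation to BC-Predict will not substantially affect screening attendance". The power claim uses the full invited groups: "With 18,700 women in each group we will have in excess of 90% power to establish equivalence", with equivalence "defined as a 95%CI on the difference which does not exceed ±5% on the attendance rate at first offered appointment".

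The Measures section describes two data streams. On one side, "Data for the nine core outcomes will be collected for each consented BC-Predict participant by the research staff". On the other, "For those in the usual care arm of the study, anonymised data will be provided by NHSBSP and FHRP services", giving overall numbers. The Participants section adds that usual-care women are not consented, that their outcomes come in aggregate, and that posters tell women being offered usual screening how to opt out.

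The Analysis plan expects 8,000 of the 18,700 women offered BC-Predict to take it up.

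**The concern.** The comparison needs outcomes for everyone invited in both conditions. The collection described covers volunteers in one condition and everyone in the other. If the analysis followed that description, the main safety question, whether the offer of BC-Predict deters women from screening, would be answered from data that tend to exclude the deterred women.

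Three features of the design make consent and attendance likely to be linked:

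- Women may join up to six weeks after the first offered appointment (Procedure), so consent can come after the outcome.
- Recruitment posters hang at the screening sites (Participants), where attenders see them.
- The information sheet tells participants that density from an attended mammogram improves the accuracy of their risk estimate (Procedure).

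The between-arm comparisons of clinic consultation, extra screening and chemoprevention also need a common denominator.

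**Working it through.** **1. The plan's own power figure.** Inputs from the Analysis plan: 18,700 per group, margin m = 5 points, two-sided 95% CI, attendance about 50% (outcome 1) and 70% (outcome 2). With true difference d = 0 and independent women:

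SE = √[p₁(1−p₁)/n₁ + p₂(1−p₂)/n₂]; power = Φ((m−d)/SE − 1.96) − Φ((−m−d)/SE + 1.96).

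- 50%: SE = 0.0052, power above 99.9%.
- 70%: SE = 0.0047, power above 99.9%.

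The stated power of more than 90% is therefore correct for the full invited cohorts. With 8,000 against 18,700 the SEs are 0.0067 and 0.0061, and power is still above 99.9% if consenters attend at the overall rate. Losing the 10,700 women costs almost no precision; the issue is bias.

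**2. Size of the bias.** Consent share f = 8,000/18,700 = 0.428, leaving 18,700 − 8,000 = 10,700 women. With no true effect:

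consenter rate − overall rate = (1 − f) × (consenter rate − non-consenter rate) = 0.572 × gap.

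A 5-point bias needs a gap of 0.05/0.572 = 8.7 points.

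**3. Effect on the equivalence test.** The article gives 69% as usual attendance. Attendance among consenters is not given, so the first column below is an assumption. The comparison is 8,000 consenters against 18,700 usual-care women, with no true effect.

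| Consenters | Non-consenters | Gap (points) | Apparent difference (points) | Power for equivalence |
|---|---|---|---|---|
| 70% | 68.3% | 1.7 | +1 | >99.9% |
| 72% | 66.8% | 5.2 | +3 | 91% |
| 73% | 66.0% | 7.0 | +4 | 38% |
| 74% | 65.3% | 8.7 | +5 | 2.5% |
| 80% | 60.8% | 19.2 | +11 | about 0 |

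**4. Masking.** Suppose the offer truly lowers attendance by 5 points, to 64% against 69%. If consenters attend at 69% and non-consenters at 60.3% (a gap of 8.7 points), the invited rate is 0.428 × 69 + 0.572 × 60.3 = 64%. The consenter-based difference is 69 − 69 = 0, so the harm disappears.

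**5. Chemoprevention (outcome 9).** The article expects 10% of 1,169 = 117 prescriptions among 8,000 consenters, and allows 0.9% among 18,700 usual-care women.

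- 117/8,000 = 1.46% against 0.9%: two-sided 5% power is about 91% with 8,000 per group, which matches the stated 90%, and about 97% with 8,000 against 18,700.
- On the invited denominator, 117/18,700 = 0.63%, below the 0.9% allowed for usual care.
- The 0.63% counts no prescriptions among non-consenters. If they were prescribed at the same 0.9%, they would add 0.009 × 10,700 = 96. That gives 213/18,700 = 1.14% against 0.9%, with power of about 64% at 18,700 per group.

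Either way, the stated 90% does not carry over to the invited comparison at a control rate of 0.9%.

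**6. The figure of more than 8,000 per group.** The Analysis plan gives this number for both the within-site and between-site comparisons. It follows directly after the 8,000 expected to take up BC-Predict and may mean consenters. It may instead mean invited women in one 8-month period, about 18,700/2 = 9,350. The text does not say which.

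**The case against.** The intended comparison is consistently by invitation, and nowhere does the article say that attendance will be analysed in consenters against all usual-care women. That data will be collected for each consented participant does not mean nothing else will be obtained, and a journal article may leave extract details to the full protocol.

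Other planned analyses also presuppose some data on invitees who do not consent. The Measures section examines uptake of services by deprivation decile of women invited. The Self-reported outcomes section compares screening uptake by allocation to questionnaires.

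A reader might infer that outcomes are collected solely for consenters, that the invited-cohort comparison cannot be built, and that volunteer bias would swamp it. The documents do not support this. The exclusivity is an inference from the sources listed. The planned analyses just mentioned suggest that invited-level data are obtainable, and the same services could supply them. A swamping bias needs both a consenter-based analysis and a large attendance gap; at 72% against 69%, power is still 91%.

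A reader might also infer that follow-up from the mammography appointment cannot apply to non-attenders. That is weak: every invitee has a first offered appointment, and outcomes 1 and 2 carry their own time anchors.

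What does not fall away is the mismatch itself. Neither of those other analyses says that the nine outcomes will be obtained for BC-Predict non-consenters. The opt-out is described only for women offered usual screening. The chemoprevention calculation has already put the consenter denominator into a between-arm contrast, which goes beyond condensed reporting.

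**Conclusion.** The concern holds as an inconsistency between the comparison defined (18,700 against 18,700 invited) and the data collection described (about 8,000 consenters against a whole cohort), with about 10,700 women unaccounted for. The stated equivalence power is correct for the invited cohorts.

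The consequence is conditional. If the described data were used for the comparison, the bias would be 0.57 times a consenter/non-consenter attendance gap that the article does not give; a gap of 8.7 points would equal the margin. For outcome 9 the mixing of denominators is already in the text and does not depend on that assumption. The calculations take 42.8% uptake as planned, treat women as independent and ignore clustering within the seven sites.

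**What to change.** - **Measures, Core outcomes:** state that the same anonymised aggregate counts from the screening and Family History clinic services will be obtained for all women invited in both conditions, consented or not. Use the same definitions, time window and opt-out, and extend the poster wording accordingly.
- **Analysis plan:** use invited denominators for every between-arm comparison. Keep consented-participant data for describing the BC-Predict pathway.
- **Power statements:** restate the chemoprevention power on a common denominator, giving the rate assumed in non-consenters, and say which women the figure of more than 8,000 refers to.

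The cost is one more aggregate extract from the same services, a line in the protocol and on the poster, and a less favourable stated power for outcome 9. No additional participants are needed.

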### Participants

Recruitment is over a 16-month period and sites will each be open to recruitment to BC-Predict for a period of 8 months. Two groups of women will be invited to participate in the study (a) women invited for first time screening (“prevalent screens”), and (b) women invited during the screening round within which they reach 60 years (“incident screens” i.e. women aged 57 to 63 years). Posters advertising the study will be displayed in each of the participating screening sites to increase awareness of the study.

We will include women who are invited for usual care (NHSBSP) at each site to compare with women offered BC-Predict; however NHSBSP women will not be consented to the study as controls, as their personal information will not be accessed. Instead, core outcome measures will be obtained in aggregated form. This will provide a comparison with uptake to these services in the BC-Predict arm. Posters at study sites will inform women being offered NHSBSP that they can request their data is not included in any analysis.

Inclusion criteria are that the participant: (a) is born biologically female; (b) is invited for first breast screening appointment (any age); is aged 57 to 63 years (only at East Cheshire and East Lancashire NHSBSP); and (c) is able to provide informed consent and complete a risk assessment questionnaire. Exclusion criteria are that the participant: (a) is born male; (b) previously had breast cancer; (c) had bilateral mastectomy; or (d) has previously participated in the PROCAS study [10].

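### Core-outcome follow-up is fixed only for consented BC-Predict women; the usual-care totals have no window, so outcomes 6-9 may be counted over unequal times

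*Protocol article*

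**What the plan says.** The protocol article, Measures, Core outcomes, contains two time rules.

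- For both groups: "The following nine core outcomes will be compared at 6-months post completion of recruitment for those offered BC-Predict and those offered usual care (NHSBSP").
- For one part of one group: the data "will be collected for each consented BC-Predict participant by the research staff for the 6 months following" the mammography appointment.

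For usual care, the same section says only that "anonymised data will be provided by NHSBSP and FHRP services, to provide overall numbers for each of the core outcomes". Under Participants, usual-care women are not consented, their personal information is not accessed, and "core outcome measures will be obtained in aggregated form".

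On timing, Participants says: "Recruitment is over a 16-month period and sites will each be open to recruitment to BC-Predict for a period of 8 months". Sites switch after the first 8 months (Study design; Setting).

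One core outcome carries an explicit window that applies equally to both groups: "Screening attendance within 180 days of episode opening" (outcome 2). Outcome 1 is tied to the first offered episode. Outcomes 6-9 (cancer diagnoses, FHRP consultation, enrolment for more frequent screening, chemoprevention) have no window of their own.

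Under Analysis plan and power calculations, Core outcomes, the groups compared are women invited to each service, and the primary method is logistic regression on binary outcomes.

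**The concern.** Outcomes 7-9, and to a lesser extent 6, can go on accruing after the screening episode. A fair comparison needs the same observation time per woman in both groups. The article fixes that time for consented BC-Predict women and leaves it open for everyone they are compared with.

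If the services supply counts up to the comparison date, usual-care women are observed for longer. Their counts of outcomes 7-9 rise and the apparent benefit of BC-Predict falls. Logistic regression on a yes/no outcome makes no allowance for unequal observation time. The planned interaction tests by time would also be mixed up with length of follow-up.

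The asymmetry is sharper for outcomes 7-9 because the BC-Predict route to them opens late within the 6 months: women with a routine recall result "will receive their risk feedback after this, approximately 6 weeks after their mammogram".

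Because the study holds only totals for usual care, it cannot shorten the window afterwards. The window has to be in the data request.

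**Working it through.** **1. The plan's own figure for outcome 9.** Inputs from Analysis plan and power calculations: 117 of 8000 prescribed chemoprevention (p1 = 0.014625), usual care at most 0.9% (p2 = 0.009), two-sided 5%, stated power 90%. Using the pooled-variance normal approximation with 8000 per group:

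- pooled p = (0.014625 + 0.009)/2 = 0.0118125
- SE under no difference = sqrt(2 × 0.0118125 × 0.9881875/8000) = 0.001708
- SE under the alternative = sqrt((0.014625 × 0.985375 + 0.009 × 0.991)/8000) = 0.001708
- z = (0.005625 − 1.96 × 0.001708)/0.001708 = 1.33, so power = 90.9%

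The stated 90% is reproduced. No time window enters the calculation, so fixing one does not change it.

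**2. Length of follow-up.** Inputs: 16 months of recruitment in two 8-month periods, and comparison 6 months later, at month 22. Assumptions: even accrual, with time counted from entry.

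- Period 1 women: 14 to 22 months, mean 18
- Period 2 women: 6 to 14 months, mean 10
- Usual care, three sites early and four late with equal throughput: (3/7) × 18 + (4/7) × 10 = 13.4 months
- Usual care, equal numbers per period: (18 + 10)/2 = 14 months
- Consented BC-Predict women: 6 months as stated

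The ratio is 13.4/6 = 2.2 or 14/6 = 2.3. If the cut were instead made 6 months after each 8-month period, usual-care follow-up would be 6 to 14 months, mean 10, a ratio of 1.7.

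**3. All invited BC-Predict women.** Only the expected 8000 of 18,700 have the 6-month window. If the other 10,700 were also counted to month 22 (assumption), their mean would be (4/7) × 18 + (3/7) × 10 = 14.6 months. The group mean would be (8000/18,700) × 6 + (10,700/18,700) × 14.6 = 10.9 months, and the ratio 13.4/10.9 = 1.2.

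**4. Effect on outcome 9.** Illustration on the basis of the plan's power statement (1.4625% among consented women). It assumes a constant usual-care rate r = −ln(1 − p6)/6, where p6 is the 6-month proportion, and follow-up spread evenly from a to b months. The expected proportion is 1 − (e^(−ra) − e^(−rb))/(r(b − a)). For p6 = 0.9%, r = 0.001507; over 6 to 22 months this gives 1 − (0.99100 − 0.96739)/(16 × 0.001507) = 2.085%.

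| Usual care at 6 months | Difference at 6 months (points) | Usual care, 6-22 months | Difference | Usual care, 6-14 months | Difference |
|---|---|---|---|---|---|
| 0.1% | +1.36 | 0.233% | +1.23 | 0.167% | +1.30 |
| 0.4% | +1.06 | 0.930% | +0.53 | 0.666% | +0.80 |
| 0.9% | +0.56 | 2.085% | −0.62 | 1.495% | −0.03 |

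At 0.1% the conclusion is untouched. At 0.4% the difference halves over 6 to 22 months. At 0.9% it vanishes or reverses.

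**The case against.** A reader might infer that the plan counts usual care to month 22, and so inflates its outcomes more than twofold. The document does not support that. Month 22 is given as the date on which both groups are compared, not as the end of accrual for usual care. It also fits a per-woman 6-month window, since it is about when the last recruits would complete one. The twofold ratio further needs a constant event rate and a 6-month window for every woman invited to BC-Predict. Only consented women have that window, and step 3 shows the ratio falling to about 1.2 on another reading. Cancers found through recall for assessment cluster near the screening episode, so outcome 6 would not grow in proportion to time. The article also expects very few usual-care prescriptions of chemoprevention, which puts outcome 9 near the top row of the table. All of this stands and limits the size of the point.

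It can also be said that an article condenses a fuller protocol, and that the services hold the records and can filter by date. The planned breakdowns by deprivation, time and location do suggest some structure in the usual-care counts. But the article is not simply silent: it states a window and gives it to one side only. The reading under which no problem arises needs a 6-month cut by the services that is nowhere stated. That any bias on outcomes 7-9 would run against BC-Predict does not remove the concern in a study whose aim is to quantify those uptakes.

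**Conclusion.** The point holds as an unmatched definition. The 6-month window covers consented BC-Predict women only. Usual-care women, and BC-Predict invitees who do not consent, have no window beyond the comparison date. If usual-care totals are taken to that date, follow-up is 6 to 22 months, mean about 13 to 14, against 6 months.

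The effect falls mainly on outcomes 7-9 and less on 6. Outcomes 1 and 2 are unaffected, and the recall counts (3-5) probably little affected. For chemoprevention the distortion ranges from trivial at a usual-care rate of about 0.1% per 6 months to decisive near 0.9%. These figures rest on even accrual and a constant event rate, neither of which the article gives. Severity is moderate: the consequence is conditional, but it cannot be undone once aggregate totals are delivered.

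**What to change.** Define outcomes 6-9 over one window for all invited women in both groups, whether or not they consent or attend. Use the same start and the same fixed length. The date of the first offered appointment is a suitable start because non-attenders also have one, whereas they have no mammogram date.

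Put this window in the data request, so that the NHSBSP and FHRP services apply it to each woman before producing totals. Set the data cut late enough for the last invited woman to complete it. Taking month 22 for everyone is not a substitute: each site would then compare a period averaging 18 months with one averaging 10, in opposite directions in the two groups of sites.

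The cost is a sentence in the protocol and a date filter in the services' counts. Stated power and sample size stay as they are.
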